## Analysis

3.

### Outcomes

3.1.

The primary trial outcome is patient completion of CRC screening at 3 years, which can be satisfied by any one of the following: colonoscopy completion at any time, negative FIT completed 2 times, or positive FIT followed by diagnostic colonoscopy within 1 year. The secondary outcomes include CRC screening completion at 3 years by any modality (to include anything satisfying the primary outcome, or completion of sigmoidoscopy, CT colonography, or MT-sDNA); the proportion of time that the patient is adherent to CRC screening process completion (during the 3 years of the study from the date of randomization); and the detection of adenomas, sessile serrated polyps, and advanced neoplasia (adenomas greater than 1 cm, or with high-grade dysplasia or villous histology, or invasive CRC). We will also evaluate the choice of screening test (colonoscopy, FIT, or other modalities) and potential screening harms such as colonoscopy perforation or post-polypectomy bleeding.

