**Methods::**

In this pragmatic randomized clinical trial, patients were randomly allocated in a 1:2:2 ratio to 1) usual care (no outreach), 2) colonoscopy only, or 3) sequential choice of colonoscopy, then fecal immunochemical testing (FIT). Patients in arms 2 and 3 were additionally randomized to receive either (a) usual care, or (b) a visit-based, clinician-directed nudge facilitated by the EHR with follow-up texting to the patient. The primary outcome is CRC screening completion within 3 years by either colonoscopy, 2 negative fecal immunochemical tests (FIT), or 1 positive FIT followed by colonoscopy within one year.

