### Eligibility and enrollment

2.2.

Using automated data extraction from the EHR database (Epic Clarity), we identified eligible patients at participating primary care practices within 30 miles of a health system endoscopy site. [31] We included patients aged 50–72 who, at the time of enrollment, were seen by primary care at least once in the past two years, were of average risk of developing CRC, and who were not up-to-date with CRC screening per guidelines at the time. [32] Patients who were not average risk were excluded, including those with a personal or significant family history of CRC, colonic polyps, Hereditary Nonpolyposis Colorectal Cancer Syndrome (HNPCC/Lynch Syndrome), other gastrointestinal cancer, gastrointestinal bleeding, or inflammatory bowel disease (Supplement Table 1). Additionally, patients who may not benefit from screening were excluded, including those with dementia, metastatic cancer, para/quadriplegia, total colectomy, those receiving hospice or palliative care, or those with an elevated chance of mortality within 3 years (Supplement Table 2). Finally, patients were also excluded if they were uninsured, had an active order for FIT (within the last 60 days) or multitarget stool DNA testing (MT-sDNA), or a positive stool test (FIT or MT-sDNA) result in the last 5 years.

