Patients randomized to a visit-based nudge arm (2B or 3B) who attend a visit with their PCP additionally receive a visit-based, clinician-directed nudge and a follow-up text 3 days post-visit. The nudges include an EHR static highlighted notification (Epic storyboard banner)(Fig. 2) notifying clinical staff (medical assistants, PCPs, and nursing staff) that a colonoscopy and/or FIT order has been placed on their behalf and encouraging discussion around completion. Patients receive a follow-up text message 3 days after the visit reminding them to follow through on active CRC screening orders (colonoscopy, FIT, or both).

Participants randomized to arm 1 (usual care) do not receive any direct outreach or visit-based nudges from this trial. Fig. 1 summarizes the trial design.

As per usual care across the health system, endoscopy reports and follow-up recommendations are provided to patients by the performing gastroenterologist, and patients completing FIT are also be notified of their results. If a FIT positive patient does not schedule diagnostic colonoscopy follow-up within two months of their result and has not received standard follow-up outreach from the practice, the research team sends a note in the EHR to population health coordinators who will provide additional support.

We will obtain baseline data from the EHR on demographics, prior CRC screening, co-morbidities, and mortality risk from automated data extraction and free text searches, as needed. We will use chart review to track outcomes of colonoscopies that are performed with polypectomy, so that we can categorize the finding. Study data are being collected and managed using REDCap electronic data capture tools hosted at the University of Pennsylvania. [37,38]

Changes in Health Maintenance (HM) status are assessed via daily Clarity query to identify documentation of screening results and determine continued outreach. All HM status changes and results (internal or external) picked up by this query are chart-reviewed and only counted toward an outcome if documentation is present in the patient chart.

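### The any-modality secondary outcome scores a positive MT-sDNA without colonoscopy as completed screening, but a positive FIT without colonoscopy as not completed

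*Protocol article*

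**What the plan says.** Section 3.1 (Outcomes) gives three routes to the primary outcome: a colonoscopy at any time, or "negative FIT completed 2 times, or positive FIT followed by diagnostic colonoscopy within 1 year". The abstract states the same condition for a positive test: "1 positive FIT followed by colonoscopy within one year".

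The first secondary outcome is "CRC screening completion at 3 years by any modality (to include anything satisfying the primary outcome", to which the section adds "or completion of sigmoidoscopy, CT colonography, or MT-sDNA". The three added tests carry no condition on result or follow-up.

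Three other places bear on the point:

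- Section 2.2 (Eligibility and enrollment) excludes patients with "a positive stool test (FIT or MT-sDNA) result in the last 5 years", so at entry the two stool tests are handled alike.
- Section 2.4 (Interventions) says that status changes and results found by the daily query are chart-reviewed and "only counted toward an outcome if documentation is present in the patient chart". This is a rule about documentation, not about the result.
- The follow-up step for positive tests in section 2.4 names FIT only: "If a FIT positive patient does not schedule diagnostic colonoscopy follow-up within two months of their result".

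**The concern.** Completion is result-dependent for one stool test and not for the other, within a single outcome. Two patients who each have a positive stool test and no colonoscopy are scored in opposite ways, depending on which test they took. No reason is given.

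The case will arise. Section 2.4 expects MT-sDNA orders during follow-up, because such an order takes an outreach patient out of the two-month reminder step. In arm 3 that step is the FIT mailing. The mix of stool tests may therefore differ by arm, with the stricter rule applying to the test that only arm 3 is mailed.

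Two things are at stake. The any-modality rate would include some patients whose screening process is unfinished by the article's own FIT standard. And if the question is settled only after the data are seen, the scoring becomes a post hoc choice.

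**Working it through.** **No stated figure to reproduce.** The article gives no expected rate, effect or power for the any-modality outcome, and no MT-sDNA rates. Its power statements concern the primary outcome, which does not include MT-sDNA.

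**Step 1: apply the section 3.1 rule to each pattern (no other qualifying test).**

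| Pattern within 3 years | Any-modality score as written |
|---|---|
| One negative FIT only | Not complete |
| Two negative FITs | Complete |
| Positive FIT, colonoscopy within 1 year | Complete |
| Positive FIT, no colonoscopy | Not complete |
| Negative MT-sDNA | Complete |
| Positive MT-sDNA, then colonoscopy | Complete (also through the colonoscopy itself) |
| Positive MT-sDNA, no colonoscopy | Complete |

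The fourth and last rows conflict. The first row shows that the outcome is not simply test uptake: a single completed FIT does not count.

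**Step 2: share of an arm affected.** All three inputs are assumptions.

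Share rescored = MT-sDNA use × positivity × proportion of positives without colonoscopy.

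- Low: 3% × 10% × 20% = 0.06%.
- High: 10% × 15% × 50% = 0.75%.

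Arm 2 has 3865 + 3870 = 7735 patients (section 2.3), so this is 0.0006 × 7735 ≈ 5 to 0.0075 × 7735 ≈ 58 patients. Anyone who also qualifies by another route would stay complete, so for given inputs these are upper figures. Wider assumptions (1-10% use, 10-20% positive, 20-50% without colonoscopy) give 1% × 10% × 20% = 0.02% to 10% × 20% × 50% = 1.0%.

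**Step 3: effect on a between-arm difference.** Only the difference in the Step 2 share matters. Suppose the arms differ only in MT-sDNA use.

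- Extreme: (10% − 3%) × 15% × 50% = 0.525 percentage points.
- Middle: a 2-point difference in use × 12.5% × 35% = 0.0875 percentage points.

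**Step 4: compare with sampling error.** Take 30% completion as a working value (the article's assumption for arm 2 on the primary outcome) and the randomized numbers: 3877 in arm 1, 7735 in arm 2, and 3867 + 3865 = 7732 in arm 3.

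- Arm 2 v arm 1: √[0.30 × 0.70 × (1/3877 + 1/7735)] ≈ 0.90 points.
- Arm 3 v arm 2: √[0.30 × 0.70 × (1/7735 + 1/7732)] ≈ 0.74 points.

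Even the extreme case in Step 3 is below one standard error of either comparison.

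**The case against.** The strongest reply is that the wording is a short parenthesis in a condensed article. It nowhere says that an MT-sDNA counts whatever its result, and a full protocol or analysis plan may hold a further rule. Counting uptake of tests that the trial does not offer could also be a deliberate, lenient choice. The tests are different modalities that the article already treats differently (two negative FITs against one MT-sDNA), and an entry exclusion does not dictate how a later test is scored.

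Part of this stands. The eligibility rule is supporting context, not proof, and a fuller document could settle the matter. But the article does state a rule, and following it produces the conflict. The uptake reading does not remove it, because one completed FIT earns no credit. Chart review means that results are seen; it does not say that they change the score.

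A reader might go further in three ways that the documents do not support:

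- *That the rule always biases against outreach, or against arm 3.* This needs MT-sDNA use to be highest in arm 1 and lowest in arm 3. No rates by arm are given. Outreach or the visit nudge could raise MT-sDNA use among patients who decline colonoscopy, and the sign could then reverse.
- *That this is the only outcome able to separate more screening from a shift between tests.* Section 3.1 also lists choice of test, including other modalities, and the proportion of time adherent.
- *That sigmoidoscopy, CT colonography and adherent days need the same correction.* The wording on the first two is equally unconditional, but the article states no result-dependent rule for a comparable test with which it would conflict. Nor does it say how MT-sDNA enters the time-adherent outcome.

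**Conclusion.** The point holds as an internal inconsistency in the definition of one secondary outcome. That conclusion rests on the text of section 3.1 and needs no assumption beyond reading completion as written.

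Its size does rest on assumptions, since the documents supply no MT-sDNA use, positivity or follow-up figures. Under the 3-10%, 10-15% and 20-50% ranges, at most three quarters of one percent of an arm would change status. The effect on a comparison would be smaller, and its direction cannot be stated. The primary outcome, its power and the multiplicity correction are untouched. The correction is worth making because it is cheap and can be made before analysis, not because it is likely to change a conclusion.

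**What to change.** In the any-modality definition in section 3.1, replace MT-sDNA with: *negative MT-sDNA, or positive MT-sDNA followed by colonoscopy within the window used for a positive FIT*. Because a colonoscopy at any time already satisfies the primary outcome, and so the any-modality outcome, *negative MT-sDNA* alone is enough. If the sponsor does intend the looser rule for MT-sDNA, the definition should say so and explain why FIT is held to a stricter one.

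This changes scoring only, not patient management. It costs one clause. The MT-sDNA result should be obtainable from the chart review already described in section 2.4. The downside is a slightly lower any-modality completion rate. The change should be fixed before the analysis that follows 3-year follow-up of all participants.

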### Sample size and power

3.2.

For the patient-directed analysis (Aim 1), after completion of the 3-year time frame for all participants, we will compare CRC screening completion for participants in each of the outreach arms, colonoscopy outreach (arm 2) and sequential outreach (arm 3), separately to the no outreach arm (arm 1); and we will also compare completion between colonoscopy (arm 2) and sequential outreach (arm 3) using intention-to-treat protocol. This includes all patients randomized, such that no evidence of completed CRC screening will be recorded as incomplete and not “missing” regardless of follow-up in the health system. Mortality will be analyzed as a screen failure but is expected to be rare and balanced by study arm. We estimate base CRC screening completion rate of 27 % in arm 1 (no outreach), which is based on estimates of response from a prior study. [29] With 20,000 patients randomly allocated in a 1:2:2 ratio, we will have 85 % power to detect a 3-percentage point increase in response rate of arms 2 and 3 relative to arm 1, and comparing arm 3 to arm 2, accounting for a total of three pairwise comparisons with a two-sided Type 1 error rate of 0.017 (Bonferroni correction of 0.05/3 = 0.017); we will also have 96 % power to detect a 3-percentage point increase in response rate for arm 3 compared to arm 2 (assuming 30 % completion in arm 2 and 33 % completion in arm 3).

For the visit-based analysis (Aim 2), we will compare the primary outcome of CRC screening completion among patients in the direct outreach arms (who have at least 1 visit with the PCP) between the usual care arm (arms 2 A + 3 A) and the visit-based nudge arm (Arms 2B + 3B) that receives clinician directed nudges during the visit and follow-up text messages. Patients in the direct outreach arms (arms 2 and 3) will be randomized in a 1:1 ratio to either receive (A) usual care/no visit-based nudge, or (B) visit-based nudge plus follow-up text. Based on retrospective analysis in this population, we estimate approximately 80 % of patients in each arm will have at least 1 visit during the course of the trial, which translates to 12,800 patients in arms 2 and 3 that will be included in the visit-based analysis (about 6400 in each arm). As this group receives direct outreach, we anticipate a 31.5 % (the average of the estimated completion rate among all patients between Arm 2 and Arm 3) response across the intervention arms for usual care (no visit-based nudges). We will have 80 % power to detect a 2.3 percentage point increase in response rates of arm B relative to arm A.

For our pre-specified subgroup analysis, we estimate 25 % of the study population (5000 patients) will be Black with a baseline completion rate of 23 %, so we will have 80 % power to detect a 5.5 percentage point increase in arms 2 and 3 compared to arm 1, and 80 % power to detect a 4.7 percentage point increase in arm 3 compared to arm 2 (assuming 28.5 % completion in arm 2). For the visit-based nudge comparison and a baseline completion rate of 30.9 % (the average of the estimated completion rate among Black patients between Arm 2 and Arm 3), we estimate that least 80 % of black patients will have at least one visit during the trial (3200 patients), and that we will have 80 % power to detect a 4.7 percentage point increase in arm B compared to arm A (estimate 4000 in arms 2 and 3 in the visit-based analysis).

Power analyses for the difference in proportions were completed in Stata/SE 16.0. While the effects of the individual interventions are seemingly modest, the additional power from the large sample size will help to determine effectiveness of different components in a multi-level intervention, as well as effect on a subgroup of Black patients who have disparities in screening outcomes. Additionally, given the relatively low cost of these interventions, even a small improvement in response could be meaningful when scaled to a large population.

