### Analytic plan

3.3.

Analysis will be conducted after completion of the 3-year time frame for all participants according to the pre-specified plan and using intention-to-treat protocol. Mortality will be analyzed as a screen failure but is expected to be rare and balanced by arm. For Aim 1, we will fit a generalized linear model (GLM) for the binomial family with a logit link, robust standard errors, and fixed effects for treatment arm and clinic to compare colonoscopy outreach to no outreach, sequential outreach to no outreach, and sequential outreach to colonoscopy outreach, separately for the primary outcome. [42] We will perform a similar analysis for the detection of adenomas, sessile serrated polyps or advanced adenomas and a zero-inflated Poisson regression model with robust standard errors for the proportion of time covered by screening tests (number of days screened). [43] We will also include socioeconomic and clinical variables in a secondary multivariable model, including age, sex, race, insurance type, income (zip code level), and prior CRC screening, along with interaction terms with the clinician directed EHR nudge assignment. This will allow us to evaluate the effect of patient outreach in the context of visit-based nudges. We will perform a subgroup analysis of Black patients for each of the primary comparisons and conduct additional subgroup analyses for non-rare subgroups in an exploratory fashion, including the same socioeconomic and clinical variables described above for all.

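### Aim 1 multiplicity and covariates: a step-down test, and adjustment for baseline variables already listed, would raise power at the same 5% family-wise level

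*Protocol article*

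**What the plan says.** Section 3.2 (Sample size and power) compares arm 2 with arm 1, arm 3 with arm 1, and arm 3 with arm 2. It describes the calculation as "accounting for a total of three pairwise comparisons" at a "two-sided Type 1 error rate of 0.017 (Bonferroni correction of 0.05/3 = 0.017"). The design inputs are: "With 20,000 patients randomly allocated in a 1:2:2 ratio"; "We estimate base CRC screening completion rate of 27 % in arm 1 (no outreach"); "85 % power to detect a 3-percentage point increase in response rate of arms 2 and 3 relative to arm 1"; and "96 % power to detect a 3-percentage point increase in response rate for arm 3 compared to arm 2". The rates behind that last figure are 30% in arm 2 and 33% in arm 3.

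Section 3.3 (Analytic plan) fits a logit model with arm and clinic for the primary outcome and makes the three comparisons separately. It names no testing procedure, so 0.05/3 for each test is the only multiplicity rule in the article. The remaining baseline variables are left to another model: "socioeconomic and clinical variables in a secondary multivariable model, including age, sex, race, insurance type", zip-code income and prior CRC screening, together with interactions with nudge assignment.

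**The concern.** Two choices give up power that could be had almost free.

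- **Multiplicity.** Holding every test at 0.05/3, whatever the other two show, ignores the logic of three arms. If arms A and B truly differ, then C cannot equal both, so at most one of the two remaining nulls is true. After a first rejection at 0.05/3, the other two can each be tested at 0.05 without the family-wise error exceeding 0.05.
- **Covariates.** The listed variables are baseline data from the health record. Age, sex, race, insurance, zip-code income and prior screening are already tabulated in Table 1. Using them as main effects in the primary model needs no new data.

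Enrolment is complete at 19,344 against the 20,000 planned, so sample size cannot recover power. The testing rule and the model still can.

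**Working it through.** **Inputs.** Planned 4000/8000/8000 (20,000 at 1:2:2). Randomized 3877/7735/7732 (section 2.3, nudge sub-arms pooled). Rates 27%, 30% and 33% (section 3.2). Prior screening 28.2% (Table 1).

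**Step 1: the plan's own figures.** Two-sided pooled z test: power = Φ[(|p2 − p1| − z·s0)/s1], where s0 is the pooled and s1 the unpooled standard error. At 0.017, z = 2.387.

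- 27% v 30%, 4000 v 8000: s0 = 0.008787, s1 = 0.008691; (0.03 − 2.387 × 0.008787)/0.008691 = 1.039, power 85.1% (stated 85%).
- 30% v 33%, 8000 v 8000: s0 = 0.007345, s1 = 0.007341; (0.03 − 2.387 × 0.007345)/0.007341 = 1.699, power 95.5% (stated 96%).

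Both reproduce.

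**Step 2: why step-down helps.** At 27/30/33 the arm 3 v 1 test (27% v 33%) has power above 99.99% at 0.05/3, so the first step is nearly always passed. Arm 2 v 1 is then in effect tested at 0.05: (0.03 − 1.960 × 0.008787)/0.008691 = 1.470, power 92.9%.

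**Step 3: simulation** (400,000 trials per setting, pooled z tests). Holm tests the ordered p-values at 0.05/3, 0.05/2 and 0.05. Shaffer tests the smallest at 0.05/3, then both others at 0.05. Rates other than 27/30/33 are sensitivity settings.

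| Rates, arms 1/2/3 (%) | N | Comparison | Bonferroni | Holm | Shaffer |
|---|---|---|---|---|---|
| 27/30/33 | planned | 2 v 1 | 85.0% | 92.9% | 93.0% |
| 27/30/33 | planned | 3 v 2 | 95.5% | 98.3% | 98.3% |
| 27/30/33 | planned | all three | 80.5% | 91.3% | 91.3% |
| 27/30/33 | randomized | 2 v 1 | 83.6% | 92.1% | 92.1% |
| 27/30/30 | planned | 2 v 1, and 3 v 1 | 85.0% | 87.3% | 89.9% |
| 27/27/30 | planned | 3 v 1 | 84.9% | 88.2% | 92.3% |
| 27/29/31 | planned | 2 v 1 | 46.0% | 60.2% | 63.0% |

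Family-wise error:

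| True state | Bonferroni | Holm | Shaffer |
|---|---|---|---|
| All arms equal | 4.4% | 4.4% | 4.4% |
| One true null (27/30/30 or 27/27/30) | 1.6–1.7% | 4.0–4.1% | 4.9–5.0% |

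All stay within 5%.

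**Step 4: covariates.** The article gives no R-squared, so a range is assumed. Replacing n by n/(1 − R²) for arm 2 v 1 at 0.017 and planned N, from 85.1%:

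| Added R² | 1% | 2% | 5% | 10% |
|---|---|---|---|---|
| Power | 85.5% | 85.9% | 87.0% | 89.0% |

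For scale, a binary predictor with prevalence 0.282 and a difference d in completion has R² = 0.282 × 0.718 × d²/(m(1 − m)). With m = 0.29, the pooled rate of arms 1 and 2, d = 10, 20 or 30 points gives about 1.0%, 3.9% or 8.9%. These differences are assumptions. The formula is not net of clinic, so it overstates the gain if prior screening varies by clinic.

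**The case against.** - **Nothing is wrong as it stands.** Bonferroni is valid, the power figures are right, and power at the randomized N is still 83.6% (2 v 1) and 94.8% (3 v 2). This stands, and it makes the point an efficiency improvement. A reader might infer that the trial is underpowered or its power statement wrong; the reproduction shows otherwise. A reader might also multiply 0.017 by three and see 0.051, but that is rounding: the article prints 0.05/3.
- **The analysis plan may already step down.** The 0.017 appears only in the sample-size section, and sizing at 0.05/3 is compatible with testing by Holm later. This stands. That the final test will be single-step is an inference from the only rule given, not something the article states.
- **Bonferroni buys something.** With one true null its realised error is about 1.7%, against 4–5% for step-down, and its intervals match its tests. The added rejections have p between 0.0167 and 0.05, where a 98.3% interval would generally include zero. This is a real cost. The extra strictness, however, is not part of the 5% the plan sets itself.
- **The gain depends on the truth.** A reader might take eight points as general. It belongs to 27/30/33. At 27/30/30 the gain is about 2 points with Holm and 5 with Shaffer, and at 27/27/30 Holm is clearly weaker than Shaffer.
- **The covariate gain is small and assumed.** The adjusted model is already planned and the primary model already contains clinic, the stratification factor. This stands as to size. It does not argue against using baseline data already in hand.

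**Conclusion.** The point holds as a recommended efficiency improvement. Against the only Aim 1 multiplicity rule in the article, a step-down test is never less powerful and keeps family-wise error at 5%. At planned N the gain on an outreach v control test is about 8 points at the design rates with either method. It is 2 to 5 points at 27/30/30, and 3 (Holm) to 7 (Shaffer) points for arm 3 v 1 at 27/27/30. These figures assume the stated control rate and simple pooled tests without covariates. The covariate step is secondary: about 0.5 to 4 points if the added R-squared is 1–10%. The documents do not support reading either choice as an error or a source of bias.

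**What to change.** 1. **Testing rule.** State for Aim 1: test the smallest of the three p-values at 0.05/3; if it rejects, test the other two at 0.05 each (Shaffer). Holm is a simpler and sometimes less powerful alternative. First settle the family: the Abstract can be read as pooling the outreach arms against no outreach, whereas sections 3.2 and 3.3 compare each arm separately.
2. **Intervals.** Report 98.3% intervals alongside, and say in advance that one may include zero when the step-down test rejects.
3. **Primary Aim 1 model.** Add age, sex, race, insurance, zip-code income and prior CRC screening as main effects beside arm and clinic. Because adjustment changes the meaning of an odds ratio in a logit model, report a standardised risk difference in percentage points. Keep the unadjusted and nudge-interaction models as secondary.
4. **Unknown values.** Fix a rule now; for race, the unknown/refused group in Table 1 (5.8%) can be its own category.

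The cost is wording in the analysis plan, fixed before the primary analysis. No new data are needed. The price is the looser link between tests and intervals, and realised error closer to, but within, 5%.
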